**Q1. Degree of uncertainty**			
	A	Effect shown	Studies show that Oroxil can reduce tinnitus.
	B	Indication of effect	Studies indicate that Oroxil may reduce tinnitus.
	B1	Indication of effect with general explanation	Studies indicate that Oroxil may reduce tinnitus. (...) The pros and cons of Oroxil cannot be fully judged, however. This requires further research.
**Q2: Type of uncertainty**			
	B1	Indication of effect with general explanation	As above
	B2	Publication bias/vested interests	Studies indicate that Oroxil may reduce tinnitus. (...) The pros and cons of Oroxil cannot be fully judged, however. The reason for this is that the company that developed the drug has not published all the studies on Oroxil.
	B3	Indirectness (population)	Studies indicate that Oroxil may reduce tinnitus. (...) The pros and cons of Oroxil cannot be fully judged, however. The reason for this is that the people who took part in the study were exposed to loud noises at work. It is uncertain whether the results also apply to other people.
	B4	Imprecision (small sample size)	Studies indicate that Oroxil may reduce tinnitus. (...) The pros and cons of Oroxil cannot be fully judged, however. The reason for this is that only a small number of people took part in the studies.
**Q3: Multiple sources of uncertainty**			
	B4	Imprecision (small sample size)	As above
	B42	Publication bias/vested interests and imprecision	Studies indicate that Oroxil may reduce tinnitus. (...) The pros and cons of Oroxil cannot be fully judged, however. The reason for this is that only a small number of people took part in the studies. Furthermore, the company that developed the drug has not published all the studies on Oroxil.
	B432	Publication bias/vested interests and imprecision and indirectness	Studies indicate that Oroxil may ease tinnitus. (...) The pros and cons of Oroxil cannot be fully judged, however. The reason for this is that the studies were small. Furthermore, the people who took part in the studies were exposed to loud noises at work. It is uncertain whether the results also apply to other people. Finally, the company that developed the drug has not published all studies on Oroxil

### Outcomes

Our primary outcome is the perception of treatment effectiveness. The secondary outcomes are subjective certainty in the judgement of treatment effectiveness, perception of the body of evidence, hypothetical treatment intention, and perception of text quality.

The perception of treatment effectiveness was measured with 1 item on an ordinal scale (*How do you judge the effectiveness of Oroxil?*) with 5 possible answers: (a) It is proven that Oroxil can help; (b) Oroxil may possibly help; (c) It is unclear, whether Oroxil helps; (d) Oroxil may not help; and (e) Oroxil definitely does not help.

Subjective certainty in the judgement of treatment effectiveness was measured on a 5-point Likert scale, ranging from *not certain at all* to *very certain*. As this relates to the first question on perceptions of treatment effectiveness, data on this item were gathered immediately after answering the first question.

The perception of the body of evidence was measured with a 6-item semantic differential (Cronbach alpha=.81), with each item measured on a 5-point Likert scale. Participants were asked to rate the body of evidence as follows:

Certain to uncertainReliable to unreliableValid to not validGeneralizable to not generalizableExcellent to poorTrustworthy to untrustworthy

The hypothetical treatment intention was measured using 1 item (*How would you decide?*) measured on a 5-point Likert scale with 2 poles: (a) definitely not take Oroxil and (b) definitely take Oroxil.

The perception of text quality was measured with a 9-item semantic differential (Cronbach alpha=.81) based on previous literature [10,11]. The construct included the following items measured on a 5-point Likert scale:

Interesting to uninterestingBalanced to 1-sidedComprehensible to incomprehensibleCredible to incredibleClear to unclearWell done to not well doneProfessional to unprofessionalAppealing to not appealingRespectable to not respectable

### Mediators (Explorative)

We collected data on the following possible mediating variables for the purpose of explorative analyses:

Decisional conflict (German version of the uncertainty subscale of the decisional conflict scale, Cronbach alpha=.76) [12]Perceived knowledge about the treatment measured on a visual analogue scale ranging from 0 for *no knowledge* to 100 for *all possible knowledge* [13]Perceived sufficiency of knowledge about the treatment for decision making, measured on an ordinal scale with 3 possible answers (more knowledge, the amount of knowledge provided, and less knowledge)Perception of the credibility of the information provider (based on previous scales, Cronbach alpha=.93) [14,15]

### Moderators (Explorative)

We collected data on the following possible moderator variables, again, for the purpose of explorative analyses:

SexAgeEducational degree based on the German school system (none/basic secondary/higher secondary/general entry qualification for university/university degree)Subjective health literacy (using the German version of the Brief Health Literacy Screening Tool (known as BRIEF), Cronbach alpha=.76) [16]Numeracy (using the 1-item version of the Berlin Numeracy Test) [17]Objective subscale of the perceived uncertainty of scientific evidence scale (Cronbach alpha=.76) [18]Medical degree or profession (yes/no)Previous experience with tinnitus (history of tinnitus/currently symptomatic/never present)

We piloted a paper-and-pencil version of the questionnaire with 2 versions of the research summary in a convenience sample of 40 students to test the reliability of the constructs, comprehensibility of instructions, the stimuli, and the questions. The reliability of the constructs was good to very good as reported above (Cronbach alpha ranging from .76 to .93). On the basis of the pretest, we omitted 2 items from the pilot questionnaire for the outcome of perceived text quality to increase reliability. We also amended the instructions to improve comprehensibility.

### Statistical Analysis

We will present demographic characteristics of the sample using frequencies, in case of categorical data, and measures of location (mean and median) and variation (SD, interquartile ranges [IQRs], and ranges), in case of continuous data.

We will treat the primary outcome variable as an ordinal scale with 5 possible values, where higher values indicate an increase in the perception of effectiveness (5=it has been proven that the treatment can help to 1=treatment definitely cannot help). We will present data as medians, IQRs, and ranges for each group. We will also present means and SDs, as well as the proportions for each possible answer in descriptive tables. This will also help to establish the practical relevance of the results.

For the secondary outcomes *perception of the body of evidence* and *text quality*, we will combine the items of each of the scales into 1 index by averaging their values, where a higher value will indicate better perception of the body of evidence or text quality.

For our confirmatory statistical analyses of the primary and secondary outcomes, we will conduct Kruskall-Wallis tests to test for overall differences between the groups within each of our 3 primary study questions. We chose to use a nonparametric test to account for the types of scales used (ordinal scaling or unequal differences between items).

In case of statistical significance, we will conduct a multiple testing procedure to perform pairwise comparisons within the groups by means of the Dwass-Steel-Critchlow-Fligner multiple comparison analysis, which is based on pairwise 2-sample Wilcoxon comparisons. All comparisons between groups across the 3 overarching study questions will be considered explorative (eg, A vs B432).

We will conduct sensitivity analyses by means of an analysis of variance (ANOVA) to test for the overall differences between the groups within each of our 3 overarching study questions. In case of statistical significance, we will conduct pairwise comparisons by means of Tukey honestly significant difference procedure. We will inspect data to ensure that they meet distributional assumptions (normality and equal variance) before applying statistical tests.

Statistical analyses will be conducted in SAS version 9.4 (SAS Institute Inc). All statistical tests will be 2-sided and performed using a 5% significance level. Where applicable, differences in means between groups will be presented together with a 95% CI. All analyses will be conducted on an intention-to-treat basis. Explorative analyses based on potential moderators and mediators are not predetermined.

As we will collect outcome data immediately after the presentation of the research summaries and panel members need to finish the questionnaire to receive an incentive, we have no major concerns regarding missing data. Furthermore, we assume that any dropouts will be likely to be missing at random, as we believe it is unlikely that the intervention has an influence on the responses to the questionnaire. Thus, we do not plan to employ any imputation methods. In case of missing data, we will present this information descriptively.

As the experiment is Web-based and participants come from a panel that provides incentives for participation, there is a risk that some participants only participate to collect their incentive and do not provide valid answers. As a measure of quality assurance, we will exclude data from participants who answer all questions in less than 2 min, spend less than 20 seconds on the page displaying the research summary, and spend less than 1.5 min between reading the research summary and completing the questionnaire (so called speeders). These time limits were determined by a priori test readings. We will also exclude participants who provide all answers in the same column for the matrix questions, that is, when more than 1 item is displayed on the screen (so called straightliners).

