**Objective:**

The objective of this study is to design an experiment to examine how different degrees of uncertainty (Q1) and different types of uncertainty (Q2) impact patients’ perception of treatment effectiveness, the body of evidence, text quality, and hypothetical treatment intention. The experiment also examines whether there is an additive effect when multiple sources of uncertainty are communicated (Q3).

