### Objectives

We are not aware of any studies investigating whether perceptions of uncertainty depend on the degree, type, or amount of uncertainty presented in written health information. Thus, we decided to address the following 3 questions in our study:

Degree of uncertainty: Do members of the public perceive treatment effects differently depending on the choice of words used to express the certainty of those treatment effects?Type of uncertainty: Do members of the public interpret uncertain treatment effects differently depending on the type of uncertainty?Number of sources of uncertainty: Is there an additive effect of multiple sources of uncertainty?

We investigated these questions using 8 variations of a written piece of hypothetical consumer health information (research summary) set in a treatment decision scenario in the context of tinnitus. The research summaries were presented to a broad group of members of the German public using a Web-based research panel. Although the study was conducted with Web-based health information, we believe the results will be applicable to all types of written health information, including printed material.

We designed the experiment as a Web-based randomized superiority study, with 8 parallel groups allocated in an equal ratio (between-group design).

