### Interventions

We chose a treatment scenario in the context of tinnitus and developed 8 variations of the research summary based on our experience and use of language in providing evidence-based health information to consumers through Germany’s statutory health website [7]. In accordance with the objectives of our study, we altered the research summary regarding the degree of uncertainty, the sources of uncertainty, and the number of sources of uncertainty. This resulted in 8 variations, two of which were used in 2 (statistically independent) comparisons (Table 1). An exemplary version of the research summary is provided in the Multimedia Appendix 1.

For the first objective of the study (Q1), we formulated 3 versions of the research summary with different degrees of uncertainty of the treatment effect. One version (A) describes a certain treatment effect and the other (B), a possible, but not certain treatment effect (indication of effect). The third version (B1) is identical to variation B but includes an additional statement on the need for further research. The semantic variations in the degrees of uncertainty of the treatment effect were based on the methods for the assessment of treatment benefits developed by the German Institute for Quality and Efficiency in Health Care (IQWiG) [8].

For the second objective (Q2), we drew on the GRADE (Grading of Recommendations Assessment, Development and Evaluation) framework to categorize different types of uncertainty. According to GRADE, uncertainty can arise from risk of bias, (unexplained) inconsistency, indirectness, imprecision, and other threats to validity, such as publication bias or vested interests [9]. We therefore formulated 3 additional variations of the research summary describing publication bias and vested interests (B2), indirectness (B3), and imprecision (B4). We will also include variation B1 in this comparison.

For the third objective of the study (Q3), we developed 2 further variations that contained a combination of 2 or 3 sources of uncertainty (B42 and B432). A variation including only 1 source of uncertainty (B4) is included in this comparison.

**Table 1 table1:** Variations of the research summary used to examine the 3 overarching research questions (translated from German).

Variations for research objective and identifier		Version	Variation in text

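### Q3 asks about an additive effect of several uncertainty sources, but its confirmatory comparisons (B4, B42, B432) cannot test additivity or separate the number of sources from which source was added

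*Protocol article*

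**What the plan says.** The Objectives section of the protocol article puts the third question as: "Number of sources of uncertainty: Is there an additive effect of multiple sources of uncertainty". The abstract repeats it as an aim of the experiment.

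The Interventions section and Table 1 define the texts compared for Q3:
- B4: imprecision (small sample).
- B42: imprecision and publication bias.
- B432: imprecision, publication bias and indirectness.

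On the single-source text the section says: "A variation including only 1 source of uncertainty (B4) is included in this comparison". The other single-source texts, B2 (publication bias) and B3 (indirectness), and the general-explanation text B1 belong to Q2.

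Under Statistical Analysis the confirmatory plan has two steps. First, "we will conduct Kruskall-Wallis tests to test for overall differences between the groups within each of our 3 primary study questions". Second, if that is significant, the plan is to "perform pairwise comparisons within the groups by means of the Dwass-Steel-Critchlow-Fligner multiple comparison analysis". ANOVA with Tukey comparisons is the sensitivity analysis. No trend, contrast or interaction is specified. For everything else a general rule applies: "All comparisons between groups across the 3 overarching study questions will be considered explorative (eg, A vs B432". B2 versus B42 falls under that rule.

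**The concern.** Additivity, in its usual meaning, compares the joint effect of two sources with the sum of their separate effects, each measured against a common reference. The Q3 set holds one of the separate effects and no reference.

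The three texts are also nested in a single order. Going from one source to two is the same thing as adding publication bias, and going from two to three is the same thing as adding indirectness. Number and identity of sources therefore cannot be told apart within Q3. This is not far-fetched: Q2 exists because the sponsor thinks the sources may be perceived differently.

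At stake is what may be concluded on one of the three primary questions. A drop from B4 to B42 could mean that two sources weigh more than one. It could equally mean that readers mind unpublished studies more than small ones and that the second source adds nothing.

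**Working it through.** **1. The plan's own figure.** For a one-way ANOVA with 4 groups, F = 0.15, alpha 5% and 159 per group, the noncentrality is 4 × 159 × 0.15² = 14.31. Power from the noncentral F distribution is 0.901, so 159 is the correct minimum for 90%. Adding 15% gives 159 × 1.15 = 182.85 per group, or 8 × 182.85 = 1462.8 in total, consistent with 1500. The sample size is not in dispute.

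**2. What additivity needs.** Write m for mean perception. Two sources are additive when (m42 − m1) = (m4 − m1) + (m2 − m1), that is, when m42 − m4 − m2 + m1 = 0. Two of the four terms, m2 and m1, lie outside Q3, so no test confined to B4, B42 and B432 can address it. As a check, 3000 simulated trials used a normal outcome with SD 1, 187 per arm, B4 = −0.20, B42 = −0.40, B432 = −0.55 and B1 = 0. Only B2 was varied (all values assumed):

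| B2 | m42 − m4 − m2 + m1 | Q3 Kruskal-Wallis rejects | Contrast test rejects |
|---|---|---|---|
| −0.20 | 0 (additive) | 85% | 5% |
| −0.60 | +0.4 (sub-additive) | 84% | 77% |
| +0.20 | −0.4 (super-additive) | 85% | 80% |

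The Q3 omnibus result carries no information on additivity.

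**3. Number versus identity.** Here the outcome had five categories (latent normal, assumed cut-points), with 187 per arm. Each non-null pattern had F = 0.15 across the three arms. For equal steps d the SD of the means is d × √(2/3), so d = 0.15/0.816 = 0.184.

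| Means of B4, B42, B432 | Kruskal-Wallis rejects |
|---|---|
| 0, −0.184, −0.367 (equal steps) | 85% |
| 0, −0.318, −0.318 (only publication bias matters) | 85% |
| 0, 0, −0.318 (only indirectness matters) | 84% |
| 0, +0.184, +0.367 (rises with more sources) | 86% |
| 0, −0.318, 0 (non-monotone) | 86% |

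The pairwise step can tell these rows apart. It cannot say whether a fall from B4 to B42 reflects two sources or the one that was added.

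**4. The full two-step plan when the worst source dominates.** Assume B4 = −0.20 and B2 = B42 = B432 = −0.54, a gap of 0.34 latent SD, on a five-category outcome with assumed cut-points. The second source then adds nothing over B2. The larger arm size is 1727/8 = 215.9, taken as 216.

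| Result | 187 per arm | 216 per arm |
|---|---|---|
| Q3 Kruskal-Wallis significant | 88–90% | 93–94% |
| DSCF: B42 lower than B4 | 75–76% | 81–82% |
| Q2 DSCF: B2 differs from B4 (further assuming B1 = 0, B3 = −0.20) | about 70% | about 77% |

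B42 versus B432 is significant in about 2% of trials, and both successive steps in about 1%.

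**5. Precision of the additivity contrast.** The SE of (B42 − B4) − (B2 − B1) is 2 × SD/√n. The 95% half-width is 1.96 × 2/√187.5 = 0.29 SD, and at 216 per arm 1.96 × 2/√216 = 0.27 SD. With 187 per arm, 80% power needs a departure of (1.96 + 0.8416) × 2/√187 = 0.41 SD. For a departure of 0.184 SD, power is about 24%.

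**The case against.** The strongest reply is that the confirmatory plan is more than an omnibus test. The DSCF comparisons of B4, B42 and B432 are confirmatory too, and so is B2 versus B4 within Q2. In the dominance scenario this fuller output would usually show no further fall at the third source, and in about 70% of trials (187 per arm) it would flag B2 against B4. This stands: the plan is informative about successive additions in the given order. It still contains no confirmatory comparison of B42 with B2.

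Second, the article never defines additive as a sum of separate effects. The question is headed by the number of sources, and it can be read as asking whether a further source has a further effect. That reading is plausible, but it too needs B42 to differ from each of its components. If it is what was meant, the wording should say so.

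Third, the additivity contrast is a poor confirmatory test. A difference of differences depends on the scale, and the sponsor chose rank tests because the scales are ordinal or unequally spaced. B1 is not a clean reference, since its text carries a call for further research that B2, B4 and B42 lack. The contrast is also imprecise. All of this stands and limits the remedy.

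A reader might also infer that the sponsor will report a significant Q3 test as an additive effect, or that B2 versus B42 was deliberately singled out for demotion. The article supports neither. It does not say how a significant result will be worded, and B2 versus B42 is caught by a general rule whose only example is a different pair.

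**Conclusion.** The point holds as a mismatch between the Q3 wording and the Q3 comparison set. The confirmatory tests can show whether adding publication bias to a small-sample statement, and then indirectness, changes perception in that order. They cannot establish additivity, and they cannot attribute a change to the number of sources. This follows from the arms and the comparison rule and does not depend on the simulations.

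The size is illustrative only. In the assumed dominance scenario, about 90% of trials give a significant Q3 test and about 75% give B42 below B4, with no gain from the second source over B2. The effect values and cut-points are assumptions, not figures from the article.

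It would go too far to say that the plan cannot inform Q3 at all, or that the data are unusable: B1, B2, B4 and B42 have all been randomized and form a 2 × 2 layout. No such layout exists for the three-source text, because there is no arm with indirectness plus only one other source. Sample size, primary outcome and choice of rank tests are unaffected.

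**What to change.** Choose one of two routes.

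**Keep a multiple-source claim.** Add B2 versus B42 to the Q3 pairwise family, and claim a multiple-source effect only if B42 is lower than both B4 and B2. Where B42 truly equals B2, a two-sided 5% test finds it lower in at most 2.5% of trials. B432 may be checked against B2, B3 and B4 in the same way. That shows only that the combination is lower than each single source. State whether the Kruskal-Wallis gate stays on B4, B42 and B432.

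Report (B42 − B4) − (B2 − B1) as a supportive estimate with 95% CI. State its scale dependence and the extra sentence in B1, and do not read non-significance as additivity.

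**Or reword.** Restate Q3 and its conclusion as whether adding further named sources to a small-sample statement changes perception, and drop the term additive.

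**Cost.** No new data are needed. If DSCF runs over all pairs, adding B2 raises the family from 3 to 6 comparisons (10 if B3 is added as well), so it is slightly more conservative. The two-part rule is demanding: an unadjusted comparison at a 0.184 SD step has about 43% power with 187 per arm, so meeting both conditions at that step is no more likely than that. Because data collection finished in May 2018, the change must be dated and disclosed as made after collection.

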### Sample Size Calculation

We based the sample size calculations for all 3 research questions on the following considerations and assumptions. We used the comparison of 4 groups (which corresponds to the second study question) as a basis and proceeded from a 1-way ANOVA with equal sample sizes in each group. We assumed a significance level of 5% and a statistical power of 90%. We decided to assume an effect size of *F*=0.15 for the primary outcome (confirmatory analysis), where *F* denotes the ratio of the SD of the group means and the common SD within each group. This decision was made based on a pretest of 2 of the research summaries, where we found small effect sizes in the range of up to *F*=0.3, depending on the outcome variable. According to Cohen, the chosen value of *F* lies between a small (*F*=0.10) and a medium (*F*=0.25) effect size [19]. Sample size calculations were conducted with nQuery version 3.0 (Statistical Solutions Ltd). This resulted in a number of 159 participants in each group. As the primary analysis is a nonparametric test, we added 15% according to a general rule of thumb [20]. To allow some leeway, we decided to randomize a total of 1500 participants, equaling an average of 187.5 participants per group.

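### The pairwise step after a significant Kruskal-Wallis test is valid but stricter than it needs to be; the critical value for k-1 groups would hold 5% within each question and find more true pairs

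*Protocol article*

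**What the plan says.** Protocol article, Statistical Analysis: the confirmatory analysis of the primary and secondary outcomes is a Kruskal-Wallis test within each study question (three groups for Q1, four for Q2, three for Q3). Then: "In case of statistical significance, we will conduct a multiple testing procedure to perform pairwise comparisons within the groups by means of the Dwass-Steel-Critchlow-Fligner" procedure (DSCF below), which is built on two-sample Wilcoxon comparisons. Only comparisons across questions are labelled explorative, so the pairs within a question belong to the confirmatory analysis. The sensitivity analysis has the same two stages, ANOVA and then Tukey. On the level: "All statistical tests will be 2-sided and performed using a 5% significance level".

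Protocol article, Sample Size Calculation: the authors took the four-group comparison and "proceeded from a 1-way ANOVA with equal sample sizes in each group", at alpha 5% and for 90% power. The assumed effect is F=0.15, where F is the SD of the group means over the within-group SD. The calculation gave 159 per group. On the allowance for ranks: "As the primary analysis is a nonparametric test, we added 15% according to a general rule of thumb". The total was then set at 1500, or 187.5 per group. No power is given for any pair.

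**The concern.** DSCF at the k-group critical value controls the familywise error within a question without any preceding test. Once a significant overall test is also required, the case in which all k groups are equal is already held at 5% by that test. In every other case at least one group differs, so at most k-1 groups can be equal and a range critical value for k-1 groups is enough. The plan keeps the k-group value and so leaves part of its 5% unused.

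This matters because the overall test says only that something differs within a question. Which degree of certainty, which type of uncertainty or which added source changes perception can be read only from the pairs. With the data collected, the analysis rule is the one place where power for those pairs can still be gained.

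**Working it through.** **1. The plan's own figure.** Inputs from Sample Size Calculation: k=4, F=0.15, alpha 5%, power 90%. The noncentrality is λ = k·n·F². At n=159, λ = 4 × 159 × 0.0225 = 14.31 and the overall F test has 90.1% power; at n=158 it has 89.9%. So 159 is reproduced. Adding 15% gives 159 × 1.15 = 182.85, or 183 per group and 8 × 183 = 1464 in total, rounded up to 1500. At n=187 the overall ANOVA power is 94.5% for four groups and 89.8% for three.

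**2. Critical values.** The critical |z| for a pair is q(k, ∞)/√2 at 5%: 1.960 for k=2, 2.344 for k=3, 2.569 for k=4. The plan therefore uses 2.34 for Q1 and Q3 and 2.57 for Q2. The k-1 step uses 1.96 and 2.34. The two-sided error per pair is 1.91% at 2.344 and 1.02% at 2.569.

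**3. Error within a question when a group differs.**
- Three groups, one differs: one true null pair remains. As written its error is 1.9%; at 1.96 it is 5%.
- Four groups, two against two: two true null pairs remain. As written, 1 - (1 - 0.0102)² = 2.0%; with k-1, 1 - (1 - 0.0191)² = 3.8%.
- Four groups, one differs: three equal groups remain. Simulation gives 2.6% as written and 4.9% with k-1.

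DSCF ranks each pair separately, so a distant group does not disturb the test of two equal groups. With one group very far away, so that the gate always opens, simulated error under k-1 is 4.9% (three groups) and 5.1% (four groups). The highest value in any run was 5.2%; with 40,000 trials the simulation standard error is √(0.05 × 0.95/40,000) = 0.11 points. With all groups equal, k-1 gives 4.7% to 4.9%.

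**4. Pair differences implied by F=0.15.** The pattern of means is not given, so a range is used. Three groups in equal steps: step = 0.15/√(2/3) = 0.184 SD, end to end 0.367 SD. Three groups, one differs: 0.15/(√2/3) = 0.318 SD. Four groups, one differs: 0.15/(√3/4) = 0.346 SD. Four groups, two against two: 2 × 0.15 = 0.30 SD. Four groups in equal steps: 0.15/√1.25 = 0.134 SD per step.

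**5. Hand check.** Adjacent pair, three groups, normal data, n=187: expected z = 0.184 × √(187/2) = 1.78. Power is Φ(1.78 - 2.344) = 29% as written and Φ(1.78 - 1.960) = 43% with k-1, before the small effect of the gate.

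**6. Simulation of the gated rule.** n=187; a five-level score from latent normals cut at -2.0, -1.2, 0 and 1.2 (assumed), scaled so that the score has F=0.15; tie-corrected tests; 20,000 to 40,000 trials per pattern.

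| Pattern | True pair | As written | k-1 |
|---|---|---|---|
| 3 groups, equal steps | adjacent | 27% | 41% |
| 3 groups, equal steps | end to end | 87.0% | 88.9% |
| 3 groups, one differs | each | 76% | 83% |
| 4 groups, one differs | each | 77% | 83% |
| 4 groups, two against two | each | 61% | 69% |
| 4 groups, equal steps | adjacent | 10% | 14% |
| 4 groups, equal steps | two steps | 49-50% | 58-59% |

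**7. What the gate itself costs.** Dropping the gate and keeping the k-group value raises the power of a pair by at most 1.2 points. The gain in the table comes from relaxing the second step.

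**The case against.** The strongest case for the plan is that nothing in it is wrong. The 159 is reproduced, the text says openly that it comes from an overall ANOVA, and an overall test followed by DSCF is a valid and common sequence. That stands. A reader might infer that the protocol claims 90% power for its pairwise answers; it makes no such claim. A reader might also infer that correcting twice is what makes pairwise power low. It is not: the gate costs about one point at most, and most of the shortfall comes from how small the pairwise differences are at F=0.15. Adjacent steps reach only 41% even under the relaxed rule, and the end-to-end pair already has 87% to 89%.

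A second objection is that the three questions are not adjusted against each other, so slack within a question is useful. Treating the questions as independent (an approximation, since B1 and B4 each serve two questions) and supposing one group differs in each, the chance of some false pair is 1 - 0.981 × 0.974 × 0.981 = 6.3% as written and 1 - 0.95³ = 14.3% under k-1. This is a real cost and should be disclosed. But the plan already accepts 5% per question, hence the same 14.3% for its overall tests when nothing differs.

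Third, k-1 has no matching simultaneous confidence intervals. That stands, but Statistical Analysis promises 95% intervals for mean differences where applicable and does not call them simultaneous.

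Fourth, the change is liberalising and data collection ended in May 2018. The analyses are written in the future tense, but the article is published retrospectively in its original format, so the tense alone does not show that results were still unseen. Timing is therefore a condition of the fix.

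**Conclusion.** The point holds as one of efficiency and reporting, not as an error. When one group differs, the rule as written spends about 1.9% (Q1, Q3) or 2.6% (Q2) of the 5% allowed within a question. The k-1 step keeps every pair that the plan would declare, because its critical value is lower. It gains about 4 to 14 points for non-extreme true pairs and about 2 for the end-to-end pair. The documents do not support a claim that the stated power is wrong, that the rule is invalid, or that all pairs are weakly powered.

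The critical values and the three-group error rates do not depend on the outcome distribution beyond large-sample normality. The power figures rest on the assumed mean patterns, the assumed cutpoints, F=0.15 and the planned 187 per group. The article reports 1727 randomized, about 216 per group (1727/8) before the planned exclusions, so the actual figures would differ somewhat.

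**What to change.** - Keep the Kruskal-Wallis gate. After a significant result, judge each pairwise Wilcoxon statistic against the studentized-range distribution for k-1 groups: the pairwise Wilcoxon test at 5% for Q1 and Q3, and the DSCF p-value computed for three groups for Q2.
- Make the same change to the Tukey step after a significant ANOVA.
- Add to Sample Size Calculation that the 90% refers to the overall four-group test and does not describe the pairs; give pairwise power for a stated range of mean patterns beside it.
- State that the 5% applies within each question, with no adjustment across the three, and that any simultaneous intervals still use the k-group value and may be slightly wider than the decisions imply.
- Fix and date the change before results by group are examined. If they have already been seen, keep DSCF as the confirmatory rule and report the k-1 results as supplementary.

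The cost is plan wording and one line of code that recomputes the p-values from the same pairwise statistics. No new data are needed.
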